#### Analysis

##### Opioid Overdose

The primary outcome, opioid-related overdose, is measured using administrative (Medicaid claims, hospital discharge data) and vital statistics. We use hospital discharge data to supplement Medicaid claims data in the event that participants lose or change Medicaid enrollment. The validity of administrative data to identify opioid-related overdose is high (sensitivity = 97%, specificity = 85%) (Green et al., 2019). We use Oregon vital statistics (death certificate data) to ascertain opioid-related fatalities. Oregon has a centralized medical examiner model which is known to provide more consistent and specific reporting of drugs implicated in fatalities (Buchanich, Balmert, Williams, & Burke, 2018; Warner, Paulozzi, Nolte, Davis, & Nelson, 2013).

Our primary analysis will examine the effect of pilot participation on the rate of fatal and non-fatal overdose events. We will calculate person-years of follow-up using the time between release date and subsequent death or study conclusion. Thus, women will contribute to calculations of person-years once they are released, except during subsequent incarcerations or after fatality. We will censor follow-up at the end of Quarter 10 or the date of incarceration if they were in prison as of this date. Our primary outcome (any opioid overdose) will be modeled as a rate with person-years as an offset variable.

We will employ either a mixed logistic model if the outcome turns out a non-rare event, or a mixed poisson model (with poisson approximation to binomial distribution) if the outcome turns out to be a rare event. The effect of ROAR participation will be examined by testing the slope coefficient (i.e., b1, see below) of the main treatment effect variable (ROAR participation yes/no) in the model. We will also adjust the treatment effect using covariates such as age, race/ethnicity, incarceration time, and mental health level of treatment need while incarcerated. We control for correlation due to clustering at county level by including a random effect (i.e., α, see below) in the model.

*Alternatively, the model described below is employed for our analysis:*

g[E(y|x)] = b0 + b1*ROAR,+b2*x + α, where g(.) is a link function (e.g., logit or log link), and b2 is a slope coefficient vector of adjusting covariates included in the model; α is the random effect account for county specificity.

As an exploratory analysis, we will investigate which baseline characteristics are associated with any overdose as our primary outcome measure, in a multivariable regression. Variables will be considered for inclusion as covariates in a final multivariable models if they are found to be associated with any overdose event in bivariate analyses at a *p* < 0.25 threshold.

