### Data collection and measures

Our primary outcome is any opioid overdose (fatal or non-fatal) within 6 months following release from incarceration. This is a binary outcome indicating a fatal or non-fatal opioid-related overdose event in the 6 months following release from incarceration. We identify fatal opioid overdose with linked vital statistics data and define fatal overdose using International Classification of Disease, 10th Revision specific codes for opioid poisoning. Non-fatal overdose is measured using Oregon Medicaid and hospitalization discharge data. We use the date of admission as the overdose date. Emergency department encounters occurring within 1 day of a hospitalization are not counted as distinct overdose events. As secondary analyses, we will examine which baseline characteristics are associated with implementation and client outcomes using both descriptive statistics as well as bivariate methods.

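### Person-years for the yes/no overdose outcome run on after a first non-fatal overdose, so the Poisson model understates first-event rates and, if ROAR works, pulls the rate ratio toward 1

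*Protocol article*

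**What the plan says.** The section on data collection and measures defines the primary outcome per woman: "This is a binary outcome indicating a fatal or non-fatal opioid-related overdose event in the 6 months following release from incarceration". The Study design section gives the same definition.

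The Opioid Overdose part of the Analysis section sets the model and the person-time:

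- The outcome goes in as a rate: "Our primary outcome (any opioid overdose) will be modeled as a rate with person-years as an offset variable".
- The clock runs from release: "We will calculate person-years of follow-up using the time between release date and subsequent death or study conclusion".
- The only interruptions are these: "women will contribute to calculations of person-years once they are released, except during subsequent incarcerations or after fatality".
- Administrative censoring: "We will censor follow-up at the end of Quarter 10 or the date of incarceration if they were in prison as of this date".
- The model is mixed logistic for a non-rare outcome, or "a mixed poisson model (with poisson approximation to binomial distribution) if the outcome turns out to be a rare event".

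The same section introduces the primary analysis as one that will "examine the effect of pilot participation on the rate of fatal and non-fatal overdose events", which could be read as counting events. No rule stops the clock at a first non-fatal overdose.

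**The concern.** A 0/1 indicator divided by person-time estimates a first-event rate only if each woman's time ends at her first event. Here a woman with a non-fatal overdose stays in the denominator until death, re-incarceration or the end of follow-up, although nothing further can be recorded for her in the numerator. The surplus time grows with the number of women who overdose, so it is larger in the group at higher risk. If ROAR lowers overdose, the comparison rate is deflated more than the ROAR rate and the estimated benefit shrinks. Absolute rates are too low in both groups whether or not ROAR works.

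The rule is stated in the text, so this is not a detail left to a later plan. It is also distinct from the question of whether follow-up ends at 6 months or at Quarter 10: cutting at 6 months makes the surplus smaller but does not remove it.

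**Working it through.** The plan gives no figure for this effect, so there is none to reproduce. Table 4 does not enter the calculation.

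**Inputs.** From Sample Size and Power: a comparison-group rate of 20% to 25% per year, and a ratio of 0.40, which is the effect on overdose mortality that the protocol cites. From the outcome definition: a 6-month window. Assumed: constant hazard; overdoses treated as non-fatal; follow-up spread evenly over 0.5 to 2 years for the longer case, because Quarter 10 is not dated.

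**Formulas.** With hazard h and follow-up T, the risk of a first overdose is 1 - exp(-hT).

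- Stated rule: rate = (1 - exp(-hT)) / T.
- Time ended at the first event: mean person-time = (1 - exp(-hT)) / h, so rate = h, the true value.

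Reading 20% and 25% per year as one-year risks gives h = -ln(0.80) = 0.223 and h = -ln(0.75) = 0.288. The ROAR hazards are 0.4 times these: 0.089 and 0.115.

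**Follow-up cut at 6 months (T = 0.5).**

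| Baseline | Comparison: stated vs true | ROAR: stated vs true | Ratio (true 0.40) |
|---|---|---|---|
| 20% | 0.211 vs 0.223 (-5.4%) | 0.087 vs 0.089 (-2.2%) | 0.413 |
| 25% | 0.268 vs 0.288 (-6.9%) | 0.112 vs 0.115 (-2.8%) | 0.417 |

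If 0.20 and 0.25 are instead taken directly as hazards, the comparison rate is 4.8% and 6.0% low and the ratios are 0.412 and 0.415.

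**Follow-up spread over 0.5-2 years (mean 1.25).** The stated rate is the average risk divided by 1.25.

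| Baseline | Average risk, comparison | Comparison: stated vs true | ROAR shortfall | Ratio |
|---|---|---|---|---|
| 20% | 0.240 | 0.192 vs 0.223 (-14.0%) | -6.0% | 0.437 |
| 25% | 0.297 | 0.237 vs 0.288 (-17.5%) | -7.6% | 0.448 |

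With hazards of exactly 0.20 and 0.25 the comparison shortfalls are 12.7% and 15.5%, and the ratios 0.433 and 0.442. A simulation with 10% of overdoses fatal, releases over 18 months and follow-up to month 30 (an assumed meaning of Quarter 10) gave ratios of 0.44 and 0.45.

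**No effect.** With equal hazards and equal follow-up both rates fall by the same fraction and the ratio is exactly 1.00.

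**Early concentration of risk.** The Background says risk is raised in the first weeks after release. If half of the first-year cumulative hazard fell in month 1, the 6-month comparison rate would be 12% (20% baseline) to 15% (25%) low and the ratio 0.42-0.43. Ending time at the first event would then give 0.39, because a single-rate Poisson model does not fit a falling hazard exactly.

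**What event-ended time does in the logistic model.** With a true hazard ratio of 0.40 and 0.5-2 years of follow-up, a logistic model with log full follow-up as offset gives an odds ratio of 0.365 (20%) and 0.356 (25%). With log time to first event as offset it gives 0.327 and 0.307. A binomial model with complementary log-log link and log full follow-up returned 0.40 in simulation.

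**The case against.** Four points deserve weight.

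1. **The larger figures arise where Poisson would probably not be used.** They imply that 24-30% of the comparison group overdoses. The plan keeps Poisson for a rare outcome, and the surplus time is small when the outcome is rare. This stands: the 6-month figures are the safer guide.
2. **Ending the clock at the event is unsafe as a blanket rule.** The offset sentence precedes the choice between logistic and Poisson, and an event-ended offset in the logistic model exaggerates benefit. This stands and limits the fix to the Poisson model.
3. **The text may mean event counts.** It speaks of a rate of events, and the measures section has a rule on distinct overdose events. If every overdose counts, the person-time rule is right. But the outcome is twice called binary, is named as any overdose, and the Poisson model is described as approximating a binomial. On the count reading those words would have to change, so an edit is needed either way.
4. **With equal follow-up the stated rule in effect estimates a risk ratio.** That is a legitimate target for a fixed window. The plan, however, calls its quantity a rate and lets person-time vary between women.

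A reader might also infer that the rule always biases the comparison toward the null, or that it costs much power. The documents do not support either. The pull exists only if ROAR has an effect. At 6 months, with 100 per group and 20% per year, simulated power was 30% against 33% with model-based errors, and 33% either way with robust errors. Over 0.5-2 years it was 65% against 73% model-based, but 72% against 73% robust. Most of that loss comes from applying Poisson variance to a 0/1 outcome.

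**Conclusion.** The concern holds for the Poisson rate model. The plan pairs a yes/no numerator with person-time suited to an event count, so first-event rates are understated in both groups, more in the group with the higher rate. For a true ratio of 0.40 the bias is small within 6 months (comparison rate about 5-7% low, ratio about 0.41-0.42) and moderate if person-time runs for 0.5-2 years (about 14-18% low, ratio 0.44-0.45). The longer case depends on an undated Quarter 10 and on Poisson still being chosen for an outcome that is no longer rare. All figures assume the plan's 20-25% per year read as one-year risks and, except for the early-risk case, a constant hazard. A share of fatal overdoses lowers the bias slightly; early concentration of risk raises it. There is no bias in the ratio when ROAR has no effect and follow-up is equal, so the rule does not manufacture a false benefit.

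**What to change.** In the Opioid Overdose analysis text, decide what the outcome is and match the person-time to the model:

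- **Yes/no outcome, Poisson rate model:** end person-time at the first opioid overdose (fatal or non-fatal), other death, re-incarceration or the end of the outcome window, whichever comes first.
- **Yes/no outcome, not rare:** do not use event-ended time as an offset in the logistic model. Use either a binomial model with complementary log-log link and log of the full potential follow-up time (not cut at the overdose, fatal or not), or a plain logistic model over the fixed 6-month window with no person-time offset.
- **All distinct overdoses:** keep the present person-time rule, define the outcome as a count, and drop the words binary and any.

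The cost is one edit to the analysis text and one derivation line. No new data are needed, since the admission date already serves as the overdose date and deaths come from vital statistics. Repeat overdoses go unused in the first two options, as they already do with a yes/no outcome.

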##### Limited Administrative Dataset

Fatal and non-fatal opioid overdoses will be assessed for all women released from prison during the 18 month study period (expected *n* = 1000) regardless of participation in ROAR. Using administrative data provided by the Oregon Department of Corrections and the Oregon Health Authority, study staff will compare odds of overdose among ROAR participants (expected n = 100) versus a comparison group of at least 100 previously incarcerated adult women with a documented SUD who are released into Oregon counties that are not participating in ROAR. Multivariate statistical analyses will be conducted to adjust for county and patient level cofounders including level of substance abuse and mental health treatment needs assessed at intake.

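### The primary outcome is a yes/no overdose within 6 months of release, but the primary analysis models a person-year rate up to an undated end of Quarter 10

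*Protocol article*

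**What the plan says.** Under Data collection and measures the outcome is fixed: "Our primary outcome is any opioid overdose (fatal or non-fatal) within 6 months following release from incarceration". The next sentence gives its form: "This is a binary outcome indicating a fatal or non-fatal opioid-related overdose event in the 6 months following release from incarceration". The Study design section repeats this definition.

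The Opioid Overdose part of the Analysis section describes something else. Its target is a rate: "Our primary analysis will examine the effect of pilot participation on the rate of fatal and non-fatal overdose events". Follow-up is open-ended: "We will calculate person-years of follow-up using the time between release date and subsequent death or study conclusion". Time in later incarcerations is removed, and the end of observation is a calendar point: "We will censor follow-up at the end of Quarter 10 or the date of incarceration if they were in prison as of this date". Then: "Our primary outcome (any opioid overdose) will be modeled as a rate with person-years as an offset variable".

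The effect measure varies as well. The Limited Administrative Dataset section says "study staff will compare odds of overdose among ROAR participants". The analysis section leaves the model to the observed frequency of the outcome: "We will employ either a mixed logistic model if the outcome turns out a non-rare event", and otherwise a mixed Poisson model. Sample Size and Power works with 20% and 25% per year, which is neither a 6-month risk nor a rate to Quarter 10.

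**The concern.** A 6-month binary outcome and an event rate over calendar-limited person-time are different quantities. They count different events, use different denominators, and answer different questions once the effect or the background risk changes over time. Both may change here. The Abstract says the injection acts for up to 1 month and that mentor support runs for 6 months after release. The Background says drug-related death risk is raised in the first 4 weeks.

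Two further features make the analysis text hard to apply as written. It names any overdose (at most one per woman) and also a rate of overdose events (possibly several per woman), and these need different person-time. It also attaches a person-years offset to an analysis that may turn out to be logistic, where such an offset does not have its usual meaning.

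At stake is the primary result of a non-randomised comparison. With two incompatible descriptions in the plan, the choice between them could be made after the data are seen.

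**Working it through.** **1. The texts side by side**

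| Item | Outcome definition | Primary analysis |
|---|---|---|
| Window | 6 months from release | release to death or end of Quarter 10 |
| Unit | woman, yes/no | rate per person-year |
| Length of follow-up | same for all | depends on release date |
| Measure | odds (Aim 2, Limited Administrative Dataset) | odds or rate ratio, by observed rarity |

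**2. Person-time outside the defined window**

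Recruitment runs from June 2019 through December 2020, about 18 months. The start of Quarter 1 is not given, so the cut-off is an assumption.
- Cut-off 6 months after the last release: follow-up 6-24 months, mean 15. Share inside the window is 6/15 = 40%.
- Cut-off 12 months after the last release: follow-up 12-30 months, mean 21. Share is 6/21 = 29%.

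**3. What the rate ratio becomes if the effect is confined to months 0-6**

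Pooled ratio = (RR × H₀₋₆ + H_later) / (H₀₋₆ + H_later), where H is the cumulative control hazard. The input RR = 0.40 is the literature figure cited under Sample Size and Power. It refers to overdose mortality and is used here only as an illustration.

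Over 15 months:
- Constant hazard: (0.4 × 0.5 + 0.75)/1.25 = 0.76.
- 0.6/yr for 1 month, then 0.2/yr: H₀₋₆ = 0.050 + 0.083 = 0.133 and H_later = 0.150, so (0.053 + 0.150)/0.283 = 0.72.
- 0.6/yr for 2 months, then 0.15/yr: H₀₋₆ = 0.100 + 0.050 = 0.150 and H_later = 0.1125, so (0.060 + 0.1125)/0.2625 = 0.66.

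Wider assumptions: 0.60 at 15 months if the hazard is three times higher throughout the first 6 months, and 0.83 at 21 months with constant hazard. If the effect persists unchanged, the ratio stays 0.40.

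**4. Power on the stated 6-month outcome**

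The plan's own figures come first. Table 4 with no clustering gives detectable differences of 0.105 (20% vs 9.5%, ratio 0.475) and 0.12 (25% vs 13%, ratio 0.52) at 80% power, 5% alpha and 100 per group. The pooled two-proportion formula

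power = Φ{[√n·|p₁−p₂| − 1.96·√(2p̄(1−p̄))] / √(p₁(1−p₁) + p₂(1−p₂))}

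gives 55% and 58% two-sided, so Table 4 is not reproduced. It rests on a simulation whose settings are not shown, and this is a separate matter. It does mean that the loss from shortening the window starts at 55-58% on this formula, not at 80%.

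6-month risk under constant hazard = 1 − (1 − annual risk)^0.5:
- 1 − √0.80 = 10.6%
- 1 − √0.75 = 13.4%

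| Annual risk | 6-month control risk | Ratio | ROAR risk | Two-sided power, n = 100 | n per group for 80% |
|---|---|---|---|---|---|
| 20% | 10.6% | 0.475 | 5.0% | 31% | 366 |
| 25% | 13.4% | 0.52 | 7.0% | 32% | 346 |
| 20% | 10.6% | 0.40 | 4.2% | 40% | 267 |
| 25% | 13.4% | 0.40 | 5.4% | 50% | 206 |

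These ignore clustering by county, which would lower power further.

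**5. How far the long window could help or hurt**

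At 20% per year, ratio 0.475 and constant hazard, a Poisson test over mean follow-up of 15 or 21 months has two-sided power of 61% or 75% if the effect persists. If the effect stops at month 6, power is 13% or 10%. The same test limited to 6 months has 29%.

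**The case against.** The strongest reply is that longer follow-up is not necessarily diluting. Study flow and SUD treatment in community let women continue the study medication or switch to another medication for opioid use disorder, so an effect could outlast mentor support. In that case the rate ratio is undiluted and the extra events raise power. This stands: a reader might infer that the planned analysis must understate the effect, and the documents do not establish that. They establish only that it targets a different quantity.

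A reader might also infer a spurious benefit from unequal follow-up: enrolment was paused in March 2020, so ROAR women could have been released earlier, be followed longer, and show a lower crude rate when risk is front-loaded. The documents do not support this as a finding. They say enrolment was paused and still plan 18 months of recruitment. If ROAR releases are assumed to end in May 2020 and Quarter 10 to end in the first half of 2021, the null ratio is 0.91-0.99. If releases continue to the end of 2020, it is 1.00-1.02. The effect is small and rests on dates the protocol does not give.

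Third, person-time after a first overdose is correct for an event count, and the protocol does have a rule for distinct events. So this is not a demonstrated wrong denominator. The fault is that the text names both an event rate and any overdose.

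Finally, the logistic option partly explains the word odds. It does not explain the person-years offset in that model, nor does it bring back the 6-month window.

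**Conclusion.** The contradiction is in the current text and needs no calculation: the outcome is a 6-month yes/no event, and the primary analysis is a rate over person-time to an undated calendar point with no 6-month limit. If the cut-off is 6 to 12 months after the last release, only 40% to 29% of person-time falls inside the defined window.

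Dilution is conditional. A ratio of 0.40 moves to about 0.66-0.76 over 15 months if the effect stops at month 6, and does not move if the effect persists. Bias from unequal follow-up is secondary and depends on assumptions. The stated power, given per year, fits neither description. On the 6-month outcome, with constant hazard and no clustering, it is about 31-32% at Table 4's effects and 40-50% at a relative risk of 0.4.

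This should be settled before analysis, because it decides what the primary result is.

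**What to change.** Make the primary analysis match the stated outcome. Count only opioid overdoses within 6 months (for example 180 days) of release, with the same cap in both groups. State one of the following as primary, with its effect measure:

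- **6-month risk:** a binary model without a person-years offset, reported as one named measure. State how death from other causes and re-incarceration within the window are handled.
- **First-overdose rate or time to first overdose:** time at risk ends at first overdose, death or day 180, with a stated rule for re-incarcerated time. This suits a wish to handle death and re-incarceration through time at risk, but it is not the binary outcome, so the outcome definition would need matching words.

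Fix the choice in advance rather than by the observed rarity of the outcome. Give Quarter 10 a calendar date and keep the event rate to that date as a secondary analysis, stating whether repeat events count. Redefining the primary outcome as a rate to a dated cut-off would also be consistent, but it changes the outcome stated in two sections and ties it to time after mentor support ends.

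Restate Sample Size and Power on the chosen 6-month scale.

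Cost: wording, one changed derivation and a new power statement. The primary analysis will have fewer events. Per 100 comparison women at 20% per year, about 10.6 have an overdose within 6 months, against about 27.9 events over a mean of 15 months (100 × 0.223 × 1.25, constant hazard). The stated power becomes less favourable, and the claim of sufficient power would have to be revised.

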Evaluate the effect of the ROAR pilot on opioid overdose among adult women released from prison. We evaluate the association between participation and the primary outcome of opioid overdose, including either a fatal or non-fatal overdose event. Fatal and non-fatal opioid overdoses are assessed for all adult females released from prison during the 18-month study period (expected *n* = 1000) regardless of participation in the ROAR intervention. Using administrative data provided by the Oregon Department of Corrections (e.g., dates of incarceration) and Oregon Health Authority (i.e., Medicaid claims and encounters), we compare the odds of overdose among participants versus a comparison group of previously incarcerated adult females with documented addiction or dependence in administrative records. Data from the comparison group will consist of de-identified administrative data for fatal and non-fatal overdoses in the state. The study will not directly recruit for this group. Statistical analyses adjust for county- and patient-level confounders including level of substance abuse treatment need and mental health treatment need assessed at prison intake.

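### The observed event frequency, with no cut-off, decides whether the primary model is logistic or Poisson, and the stated person-years offset is not confined to the log link, although it is invalid under a logit link

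*Protocol article*

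**What the plan says.** *Data collection and measures* defines the primary outcome: "This is a binary outcome indicating a fatal or non-fatal opioid-related overdose event in the 6 months following release from incarceration". The study design text under Fig. 1 says the same.

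The *Opioid Overdose* analysis section then makes four statements about the model:

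- Offset: "Our primary outcome (any opioid overdose) will be modeled as a rate with person-years as an offset variable". This comes before the choice of model and exempts neither branch.
- Choice of model: "We will employ either a mixed logistic model if the outcome turns out a non-rare event, or a mixed poisson model", the latter "with poisson approximation to binomial distribution) if the outcome turns out to be a rare event". No threshold separates rare from non-rare.
- Equation: intercept, ROAR term, covariates and a county random effect, "where g(.) is a link function (e.g., logit or log link"). No offset is printed.
- Follow-up: person-years run from release to death or study conclusion, leaving out time back in prison, and "We will censor follow-up at the end of Quarter 10 or the date of incarceration if they were in prison as of this date".

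Elsewhere the comparison is put in terms of odds. Aim 2 says "we compare the odds of overdose among participants versus a comparison group", and *Limited Administrative Dataset* says "study staff will compare odds of overdose among ROAR participants".

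**The concern.** Two things are fixed badly here; they are not merely left for a later document.

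First, the model for the single primary test is chosen after the outcome is known, by an undefined criterion. The planning rates in *Sample Size and Power* are 20% to 25% per year, or roughly 10% to 13% over six months. At that level either branch could be argued. The branch decides whether the result is an odds ratio or a rate ratio.

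Second, read literally, the offset applies to whichever model is chosen. A log person-time offset makes the modelled quantity proportional to time. That is right for a rate under a log link and wrong for odds under a logit link. The logistic branch is reserved for non-rare events, which is where odds and rate diverge most. If follow-up differs between ROAR participants and the comparison group, the ROAR coefficient can depart from zero with no effect at all.

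**Working it through.** **Inputs.** From the article: a baseline rate of 20% per year and 100 women per group (*Sample Size and Power*, Table 4); a 0/1 outcome; variable person-time. Assumed for this check: a constant hazard, no county clustering, and every follow-up length below. The article has no figure for the offset issue that could be reproduced first.

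**1. Odds against time.** Hazard λ = −ln(1 − 0.20) = 0.2231 per year; p(t) = 1 − exp(−λt); odds(t) = p/(1 − p).

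| t (years) | p(t) | odds | odds / t |
|---|---|---|---|
| 0.5 | 0.1056 | 0.118 | 0.236 |
| 1.0 | 0.2000 | 0.250 | 0.250 |
| 1.5 | 0.2845 | 0.397 | 0.265 |
| 2.5 | 0.4276 | 0.747 | 0.299 |

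A logit model with a log(t) offset assumes that the last column is constant. It rises by 0.299/0.236 = 1.27 between 0.5 and 2.5 years.

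**2. Null bias when follow-up differs.** With the same hazard in both groups, the apparent ratio is [odds(T1)/T1] / [odds(T2)/T2].

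| Assumed follow-up, T1 vs T2 (years) | Apparent ratio (truth 1.00) |
|---|---|
| equal | 1.00 |
| 0.50 vs 0.45 | 1.006 |
| 1.5 vs 1.4 | 1.012 |
| 1.5 vs 1.0 | 1.060 |
| 2.0 vs 0.75 | 1.158 |

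The group followed for longer looks worse.

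**3. Fitted models.** Very large simulated samples (400,000 per group), with a log person-years offset and follow-up uniform over assumed ranges:

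| Follow-up, comparison / ROAR (years) | True hazard ratio | Logit + offset | Complementary log-log + offset |
|---|---|---|---|
| 1–2.5 / 1–2.5 | 1 | 0.99–1.01 | 1.00 |
| 1–2.5 / 1–2.5 | 0.475 | 0.43 | 0.47–0.48 |
| 1–2.5 / 0.5–1.5 | 1 | 0.92 | 0.99–1.01 |
| 1–2.5 / 0.5–1.5 | 0.475 | 0.41 | 0.48 |

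With equal follow-up distributions the null is preserved, but a true 0.475 is still read as 0.43. When follow-up varies between women, the logit coefficient is neither an odds ratio nor a rate ratio.

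**4. Poisson branch (minor).** A model-based Poisson variance for a 0/1 outcome omits the factor (1 − p). Under the null the standard error is therefore too large by 1/√(1 − p): 1.026 at 5%, 1.054 at 10% and 1.069 at 12.5% risk. The large-sample type I error is 2Φ(−1.96/√(1 − p)) = 0.044, 0.039 and 0.036 respectively. Exact enumeration of 100/100 tables at 10.6% vs 4.2%, with Wald tests on the log risk ratio, gives power 0.309 with Poisson variance and 0.336 with binomial variance, a cost of about 3 points.

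**The case against.** The strongest reply is that logit with an offset is only one reading of inconsistent text. The printed equation has no offset, the comparison women are released over the same period as participants, and one censoring rule covers both groups. If follow-up is equal, or is held to six months with only short interruptions, the null bias is zero or negligible (1.006 for 0.50 vs 0.45 years). This stands as a limit on size. It does not remove the defect: the offset sentence covers the primary outcome without exception, and person-years run to Quarter 10, so variable follow-up is part of the plan.

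A reader might infer three stronger points that the document does not support:

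- *That the switch inflates type I error.* Choosing a link from the overall event frequency is not choosing it from the group contrast, and no inflation has been shown. Nor is it an error that 0.25 vs 0.13 gives a risk ratio of 0.52 and an odds ratio of 0.45; both describe the same table correctly. The fault is that the plan does not say which will be reported.
- *That the logistic result will be off by 6% or 16%.* Those figures rest on assumed follow-up gaps.
- *That the Poisson branch will give standard errors much too wide and a large loss of power.* The article names no variance estimator, and a condensed article may leave that to the analysis plan. The branch is also reserved for rare outcomes. Large losses appear only at 20% to 25% risk, or when a Wald test is set against a different kind of test.

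**Conclusion.** The point holds in two parts. The primary model and its effect measure are left to an undefined judgement of rarity made on the observed outcome. The offset statement, taken with the logit option, also permits a model whose coefficient has no clean interpretation once follow-up varies. The article's own wording is split between odds, a rate, and a binary outcome at six months.

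The non-proportionality of odds to time follows from the article's 20% per year under a constant hazard. The size of any bias in the trial is unknown: nil under the null if the groups have equal follow-up, about 1% to 16% across the gaps of 0.1 to 1.25 years assumed above. The Poisson variance is a minor, conservative matter, with type I error of about 3.6% to 4.4% in large samples at 5% to 12.5% risk. This should be corrected, but it does not by itself invalidate the evaluation.

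**What to change.** Before outcome data are linked, delete the rare/non-rare switch and the logit-with-offset option, and name one model, one effect measure and one time window.

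- For the binary 6-month outcome as defined: log-link (modified) Poisson regression with robust variance and no offset, reported as a risk ratio.
- If time at risk must be accounted for: either a complementary log-log model with offset log(potential time at risk, capped at 6 months), or Poisson or Cox regression on time to first overdose, reported as a hazard or rate ratio. The complementary log-log offset must be potential time at risk; using time to first overdose there introduces its own bias.

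If the Poisson branch is kept for the 0/1 outcome, state robust variance. Bring the odds wording in the Abstract, Aim 2 and *Limited Administrative Dataset*, and the printed equation, into line with the choice. The cost is one paragraph of wording and standard software, with no change to data collection.
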